## Abstract

**Background:**

Evidence from pilot trials suggests that structured learning techniques may have positive effects on the performance of cognitive tasks, movement sequences or skills in patients with Alzheimer's disease. The purpose of this trial is to evaluate whether the usual method of learning by trial and error or the method of errorless learning demonstrate better effects on the performance of two selected daily living tasks six weeks after the intervention in people with mild to moderate dementia.

**Methods/Design:**

A seven-centre single-blind, active-controlled design with a 1:1 randomisation for two parallel groups will include 175 persons diagnosed with Alzheimer's disease or mixed type dementia (MMSE 14-24), living at home, showing at least moderate need for assistance in instrumental activities of daily living; primary carer available and informed consent of patient and primary carer. Patients of both study arms will receive 15 one-hour-sessions at home by trained interventionists practising two daily living tasks individually selected. In one group the trial and error technique and in the other group the errorless learning method will be applied. Primary outcome is the task performance measured with the Task Performance Scale six weeks post treatment.

**Discussion:**

The trial results will inform us to improve guidelines for instructing individuals with memory impairments. A user-friendly practice guideline will allow an efficient implementation of structured relearning techniques for a wide range of service providers in dementia care.

**Trial registration:**

DRKS00003117

## Background

Dementia is a neurodegenerative progressive disease with high prevalence and incidence rates and enormous costs for international societies [1-7]. Consequences of dementia are an increasing deterioration of patients' daily functioning and a high burden mainly borne by the primary carers or nursing staff in nursing homes and in the community [8-10]. Relearning of relevant daily-living tasks in dementia has the potential to stabilise the daily functioning of people with dementia and to increase their independency. Alzheimer's Disease (AD) alters memory and learning to such a degree that it heavily interferes with daily living. Normally, learning occurs in an unstructured manner by trial and error, which consists of guessing and the occurrence of errors during acquisition. Errorless learning is a teaching technique using feed-forward instruction, in order to prevent people from making mistakes during the learning process. In AD patients, the amount of such errors may be reduced by providing adapted cues prior to performing the target task and limiting the patient's guessing [11].

Evidence from small-scaled pilot trials suggests that errorless learning techniques may have positive effects on the performance of cognitive tasks, movement sequences or skills in patients with AD [11-17]. A meta-analysis found large effect sizes in favour of errorless learning (d = 0.87, p = 0.008) [18]. The Nijmegen research group compared the effects of learning strategies on activities of daily living in a pilot trial with 12 AD patients from nursing homes and day care centres. Patients in the errorless learning group significantly improved their performances with large effect size after six sessions (η^2^_p _= 0.8, p < 0.01) and at delayed assessment (η^2^_p _= 0.5, p = 0.01) [19]. These preliminary data show that people with AD can relearn tasks they were not able to perform before. However, the results need to be replicated at a larger scale and within the patient's familiar environment.

Therefore, the purpose of our multi-centre REDALI-DEM study is to evaluate whether the usual method of learning by trial and error (TEL) or the method of errorless learning (ELL) demonstrate better effects on the performance of two selected daily living tasks six weeks after the intervention in people with mild to moderate dementia living at home. Secondary research questions are:

• Can effects on performance be maintained 3 months post treatment?

• Does relearning of two relevant daily living tasks show any generalising effect on the patients' initiative or need for assistance in activities of daily living?

• Costs and practicability of as well as patients' satisfaction with treatment.

## Methods/Design

To compare the effects of errorless and trial and error learning, we used a seven-centre single-blind, active-controlled design with a 1:1 randomisation for two parallel groups. The study has been registered at the German Trial Register (No. DRKS00003117, available at http://apps.who.int/trialsearch). The Medical Ethics Committee of the University Hospital Freiburg has given ethical approval (No. 194/11).

### Participants and setting

#### Inclusion criteria

• Persons diagnosed with Alzheimer's disease or mixed type dementia.

• Mini Mental State Examination: 14-24.

• Living at home.

• Carer available for rating the need for assistance in activities of daily living.

• At least moderate need for assistance in instrumental activities of daily living; mean score of the five household items in the performance scale of the Interview for Deterioration in Daily Living Activities in Dementia must be 2 or higher.

• Informed consent of patient and primary carer.

#### Exclusion criteria

• Major depression, Geriatric Depression Scale (15 items) ≥ 9.

• Major need of physical nursing care (level 2 or higher according to the German Long-Term Care Insurance Act indicated by 120 min or more per day).

• Severe behavioural disturbances, unstable medical conditions or lack of attention and understanding of simple task instructions in German language, which do not allow participation in the study as judged by the recruiting study physician.

• Involvement in other clinical trials.

• In order to achieve the recruitment of a naturalistic sample, there will be no limitation on drug therapy. During the trial duration, drug treatment should be kept as constant as it is appropriate for an optimal routine medication management. Within the statistical analysis, we will control for possible changes in anti-dementia drug treatment in both groups.

#### Setting

REDALI-DEM study centres are five outpatient memory centres at university hospitals in Bonn, Freiburg, Mainz, Marburg and Tübingen; one Department of a municipal hospital in Stuttgart specialising in geronto-psychiatry; and a centre for psychiatry in Emmendingen. The centres are located throughout Germany in urban regions and have all provided outpatient dementia care for five to seventeen years. Their standard service comprises diagnostic work-up for dementia and related diagnoses as well as recommendation of risk reduction, dementia medication and non-pharmacological treatments. Principal investigators of the centres are psychiatrists or neurologists with eight to fifteen years of experience in dementia care. We will control for possible site effects.

### Intervention

#### Intervention scheme

1. The scheme for the ELL and TEL intervention is divided into two blocks (table 1). The first block consists of 12 sessions within 10 weeks, the second block includes 3 refresher sessions within two weeks.

**Table 1 T1:** Intervention scheme

Weeks	0	1-10	11	16*	19-20	26
Measurement time points	**t**_**0**_		**t**_**1**_	**t**_**2**_		**t**_**3**_
Intervention		12 sessions		break	3 refresher sessions	

* Primary measurement time point

2. In the first block, the general scheme is 2 sessions per week, with following exceptional cases: When patient is ill or not available, protocol allows

a. maximum 4 weeks without session in total

b. maximum 3 sessions per week are allowed to catch up on the missing sessions

3. In the second block, 3 refresher sessions must be performed within two weeks.

4. In order to avoid contamination, ELL and TEL interventions are delivered by separate interventionists and the seminars on ELL and TEL interventions are separated.

5. Each study-site has three interventionists, in order to avoid that more than 21 interventionists are to be instructed. At least one interventionist must be an occupational therapist. The other interventionists can be trained from another professional background in the medical field, e.g. psychology or nursing. Their curriculum vitae must indicate professional experience with or special qualification for geronto-psychiatric patients. Each site has one main ELL interventionist, one main TEL interventionist and one substitute interventionist, who must substitute both, the ELL and TEL interventionist. The ELL interventionist is not allowed to attend the seminar on the TEL intervention and vice versa. The substitute interventionists must attend both seminars, TEL and ELL. Maximal 5 treatment sessions per patient (33%) can be applied by the substitute, in order to reduce the contamination rate.

6. In order to reduce bias by systematic selection, interventionists of each study site are assigned by random to be ELL or TEL interventionist.

#### Intervention sessions

Baseline session (same procedure in ELL and TEL group)

1. Selection of two tasks

Together with the patient and the carer, the interventionist determines two tasks to be relearned based on following criteria:

a. Tasks are from a pre-structured pool of IADL tasks, such as changing batteries, folding a t-shirt, setting a table, using a coffee machine. This pool consists of 20 IADL tasks, each of it structured in single task steps.

b. The patient and the carer confirm that the patient (1) was used to regularly perform the tasks within the last year, (2) that he is not able to do so anymore and (3) that he is still interested in. It must be clear that the patient himself is motivated to do the tasks again and that this motivation is not primarily driven by the carer's interest.

c. The interventionist asks the patient to try to perform the tasks without cue and can clearly observe that the patient is not able to perform the tasks without errors.

2. Video tapes of baseline task performance

a. Task I: The interventionist asks the patient to perform task I. The interventionist video records the performance without giving any verbal cue or instruction.

b. Task II: The same procedure.

Relearning sessions are scheduled for a total of 120 min. It is not intended to involve the carer during the relearning sessions.

1. The **ELL **condition consists of the following procedures.

a. The interventionist provides the patient with a special cue card series depicting each task step.

b. He asks the patient to perform the task step by step.

c. As soon as the interventionist anticipates that the patient could make an error, he intervenes and again gives brief verbal instructions or short demonstration as cues for the correct performance.

d. When the patient has performed the first step correctly, the interventionist gives instruction for the next step.

e. These procedures of interventionist's instruction, patient's performance and interventionist's early intervening for avoiding errors are followed until the whole task is performed.

f. However, the training will stop after 30 min, no matter how many steps of the task the patient has performed without error. When the patient shows errorless performance of the whole task in less than 30 min training, the same task is trained again, but not more than twice.

2. The **TEL condition **consists of the following procedures.

a. The interventionist asks the patient to perform the task. Cue cards are not provided.

b. When the patient makes an error, he is allowed up to three guesses (or a maximum of 30 seconds without guess) to correct on his own.

c. If the participant is unable to perform the step correctly, the interventionist will use different questions relative to the purpose of the task, in order to help the patient to find solutions.

d. If the participant is still unable to perform the step correctly, the interventionist will give the correct verbal instruction - but no demonstration - of what is to do next, so that the patient can perform the step correctly.

e. These procedures of patient's performance incl. guessing, interventionist's helping questions and - if necessary - correct instructions are followed until the whole task is performed.

f. The training will stop after 30 min, no matter how many steps of the tasks the patient has performed. When the patient performed the task in less than 30 min training, the same task is trained again, but not more than twice.

Final intervention session (same procedure in ELL and TEL group)

Video tapes of baseline task performance

a. Task I: The interventionist again video records the performance without giving any cue or instruction.

b. Task II: The same procedure.

Assessment sessions

The interventionist must video record the patient's task performance at measurement time point T_2 _(16 weeks after baseline) and T_3 _(26 weeks after baseline). In the assessment visits, he has to follow the same procedures as in the final intervention session.

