### Outcome

The primary outcome is the performance of the two selected and trained daily living tasks. The applied measurement is the Task Performance Scale. It demonstrated feasibility and responsiveness within the pilot trial. The evaluation of task performance by measuring the number of occurring errors or the number of insufficient task performances is an established standard in trials on relearning cognitive or daily living tasks. Patient's task performance will be video recorded by the interventionist, in order to assure blinded rating and to avoid that the patient will have potentially confusing contacts with several different persons. Blinded assessors from the REDALI-DEM headquarters in Freiburg will rate the videos regarding the number of occurring errors and steps performed insufficiently. Table 2 shows the primary and the secondary outcomes including measurement instruments and time points. Secondary outcome and control measures are performed by the study physician during the patient's visit at the study site, except the Verbal Rating Scale for the satisfaction with the intervention, which is applied by the interventionists at the patient's home.

**Table 2 T2:** Measurement scheme including primary and secondary outcome

Weeks	0		11		16*		19-20		26
Measurement time points	t_0_		t_1_		t_2_				t_3_
Intervention		12 sessions		break		break	refresher	break	
Primary outcome									
Task Performance Scale (Rating of assessment video)	x		x		**x**				x

Secondary outcomes									
Satisfaction with intervention (Verbal Rating Scale)		each session					each session		
Activities of daily living (Interview for Deterioration in Daily Living Activities in Dementia)	x				**x**				x
Resource utilisation (Resource Utilisation in Dementia)	x				**x**				x

Control measurements									
Cognition (Mini Mental State Examination)	x				x				x
Course of Dementia (Clinical Dementia Rating)	x				x				x
Challenging behaviour (Neuropsychiatric Inventory, 12 items questionnaire)	x				x				x
Socio-demographic data	x								
Depression (Geriatric Depression Scale, 15 items)	x								
Attention (Trail Making Test)	x								
Intervention adherence (rating of treatment videos)		selected sessions							

* Primary measurement time point

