### Randomisation and Blinding

The trial statistician at a detached site will provide a 1:1 randomisation block-wise without stratification via e-mail for each individual case after recruitment and upon request of the site investigator. Independent assessors are blinded to group assignment. Following the nature of the intervention, participants are not blind for the type of intervention. However, neither the patients nor the interventionists will be explicitly presented an assumption as to which intervention may be more likely to improve activities of daily living. Moreover, both interventions include the same amount of personal involvement which prevents contrasting interventions with waiting group scenarios or grossly reduced personal involvement. Blinded assessment of the treatment effects will be achieved by videotaping the performance of the patient and removing all hints of prior treatment modality.

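### On the natural reading, an interventionist who knows the arm helps choose the two outcome tasks and films baseline; these steps should come before allocation

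*Protocol article*

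**What the plan says.** **Who does what at baseline (Intervention sessions).** On task choice the article states: "Together with the patient and the carer, the interventionist determines two tasks to be relearned based on following criteria". The tasks come from a pool of 20. Patient and carer must confirm earlier regular performance, present inability and continued interest. The interventionist then asks for an uncued attempt and "can clearly observe that the patient is not able to perform the tasks without errors". The t0 recording follows: "The interventionist video records the performance without giving any verbal cue or instruction". The session is headed "Baseline session (same procedure in ELL and TEL group".

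**Who the interventionist is (Intervention scheme, items 4 to 6).** "ELL and TEL interventions are delivered by separate interventionists". On staffing: "Each site has one main ELL interventionist, one main TEL interventionist and one substitute interventionist". The substitute attends both seminars. Interventionists are assigned to a method at random.

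**When allocation is issued (Randomisation and Blinding).** The statistician sends it by e-mail "for each individual case after recruitment and upon request of the site investigator". The assessors who rate the videos are blinded. Nothing is said to blind the person who selects the tasks and films.

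**What depends on it (Outcome; Sample Size, Reasoning).** The primary outcome is performance of the two selected tasks, and the primary endpoint is the interaction of group with T0 and T2.

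**The concern.** The two tasks are the content of the primary outcome, and the t0 video supplies one of the two time points in the primary contrast. If both are settled by someone who knows the arm, they may be influenced by allocation. There are two routes:

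- **Task choice.** Tasks that respond better to one method could be chosen more often in that arm. Blinded rating scores whatever was chosen and cannot undo the choice.
- **The t0 attempt.** The way the first attempt is elicited could differ by arm, which would move the baseline score.

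The Intervention adherence section adds to the first route. Training in how each task is broken into steps and cued is listed only for ELL interventionists and substitutes, so those who select tasks differ by arm in what they know about them.

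**Working it through.** **Order of steps, from the text.** No passage places task selection or the t0 video before allocation. Three points suggest the reverse:

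1. The baseline session is listed among the intervention sessions and described by group.
2. Both seminars teach how to involve patients in selecting tasks, so ELL and TEL interventionists are both expected to do it.
3. The Outcome section has the interventionist film partly so that patients do not meet several different people. If a main interventionist ran baseline before a 1:1 allocation, about half the patients would then change interventionist, against that aim.

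**The plan's own figure.** Inputs from Sample Size: N = 160, f = 0.10, correlation 0.6, two measurements, alpha 5%.

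- λ = N × f² × m / (1 − ρ) = 160 × 0.01 × 2 / 0.4 = 8.00, with df 1 and 158, critical F 3.901 and power 80.3%.
- N = 158 gives 79.8%, so 160 is the smallest even total that reaches 80%. The stated figure reproduces.
- The detectable difference in change is 4 × f = 0.40 SD.

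**Sensitivity to an assumed shift b** (80 per arm, no true effect, normal approximation; the documents give no value for b).

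*Change contrast T0 to T2.* SD of change = √(2 × (1 − 0.6)) = 0.894 SD. SE = 0.894 × √(2/80) = 0.141 SD. The test statistic moves by b / 0.141.

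*Baseline as covariate, shift only in the t0 video.* Bias = 0.6 × b. SE = √(1 − 0.36) × √(2/80) = 0.8 × 0.158 = 0.126 SD.

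| Assumed b (SD) | Share of 0.40 SD | Type I error, change contrast | Type I error, baseline as covariate |
|---|---|---|---|
| 0.05 | 12.5% | 6% | 6% |
| 0.1 | 25% | 11% | 8% |
| 0.2 | 50% | 29% | 16% |

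The last column applies only to a shift confined to the t0 video. A shift in trainability appears at T2 and not at T0, so adjusting for baseline leaves it in place.

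**The case against.** The strongest reply is that the article never says the session follows allocation. The trial-flow figure is not shown, and a condensed article may leave the exact order to the full protocol. A reader might take the timing as stated. It is an inference, though the likeliest one from what is written.

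The safeguards are also real:

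- The pool is closed, and the confirmation criteria cut it down for each patient, so the interventionist does not pick freely from 20 tasks.
- The patient must be the one who is motivated.
- The attempt and the filming are uncued and the same in both arms.
- Training in the pool and in selection is common to both seminars, which standardises it. The separation of the seminars is therefore not evidence of bias in itself.
- Interventionists are assigned to method at random and are not told which method is expected to do better.
- Baseline imbalance will be adjusted for.

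These points limit the problem, and they rule out saying that randomisation no longer protects the comparison. They do not close the gap. The interventionist still takes part in the choice and judges failure. Random assignment of interventionists does not hide a patient's arm, and adjustment does not reach trainability.

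A reader might also infer that the allocation e-mail unblinds the physician who assesses the secondary outcomes, since "Secondary outcome and control measures are performed by the study physician". The documents do not establish this. They do not identify the requesting site investigator with that physician, and carers supply the ratings of need for assistance. It forms no part of this point.

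**Conclusion.** The point holds as a weakness in the design as described, and it should be fixed. It rests on one inference, that selection and filming follow allocation, and on the stated facts that the main interventionists are arm-specific and that blinding is described only for the video raters. On that reading, protection of the primary group-by-time comparison is weakened.

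The documents give neither the size nor the direction of any bias. The error rates of about 8–11% at 0.1 SD and 16–29% at 0.2 SD show how sensitive a trial planned for a small effect would be. They are not estimates of what will happen, and a reader should not take them as evidence that the result will be biased. No stated number is wrong, and the sample size is unaffected.

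**What to change.** State and enforce the order: both tasks selected, both t0 videos recorded and both logged, and only then the allocation requested. Have the site's substitute interventionist, already in post and trained in both methods, run that visit. The person choosing and filming then cannot know the arm, and patients are not started with one main interventionist and moved to the other.

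The cost is one reassigned home visit per patient, about 175 / 7 = 25 per site. There are two drawbacks. Each patient has one additional contact, which runs against the article's aim of few different contacts for people with dementia. The t0 attempt is also elicited by a different person from T2, though equally in both arms. Sample size, treatment and outcome definition stay as they are. If the full protocol already sets this order, one sentence in the Randomisation and Blinding section saying so would settle the timing.
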